## Abstract

**Background:**

Metabolic syndrome (MetS) is a group of risk factors that increase the risk of death and a variety of chronic diseases. Recent studies have indicated that the imbalance of gut microbiota might contribute to development and progression of metabolic syndrome. Carbohydrate restriction in the diet has been proven to be one of the most effective methods in the management of metabolic syndrome, even in the absence of weight loss. However, no study has examined the effects of a carbohydrate-restricted diet on gut microbiota composition in metabolic syndrome patients. Thus, we will examine the effects of a “moderately restricted carbohydrate (MRC)” diet on gut microbiota, insulin resistance, and components of MetS among Iranian women. In addition, the stability of changes in dependent variables, including gut microbiota, will also be assessed.

**Methods:**

This is a parallel randomized clinical trial in which 70 overweight or obese women aged 20–50 years with MetS will be randomly assigned to receive either MRC diet (42–45% carbohydrate, 35–40% fats) or a normal weight loss (NWL) diet (52–55% carbohydrate, 25–30% fats) for 3 months. Protein accounted for 15–17% of total energy in both diets. The quantity of gut microbiota including Firmicutes, Bacteroidetes, *Bifidobacteria*, *Lactobacillus*, *Clostridium*, *Prevotella*, *Bacteroidetes*, and *Akkermansia muciniphila*, as well as anthropometric, blood pressure, and metabolic parameters will be measured at study baseline and the end of trail. At the end of this phase, all participants will be placed on a weight maintenance diet for an additional 6 months. After following up study subjects in this duration, all dependent variables will be examined again to assess their stability over this period.

**Discussion:**

To the best of our knowledge, this is the first randomized controlled trial investigating the effects of a moderately restricted carbohydrate diet on gut microbiota composition and several metabolic parameters during the weight loss and maintenance phases in women with MetS.

**Trial registration:**

Iranian Registry of Clinical Trials (www.irct.ir, IRCT20210307050621N1). Registered on May 31, 2021.

**Supplementary Information:**

The online version contains supplementary material available at 10.1186/s13063-022-06922-5.

## Background

Metabolic syndrome (MetS) is a group of metabolic abnormalities that include hyperglycemia, hypertension, elevated triglyceride levels, low HDL cholesterol levels, and abdominal obesity. Each of these abnormalities contribute to an increased risk of developing a variety of non-communicable diseases and mortality [1, 2]. The prevalence of metabolic syndrome is increasing as obesity rates rise globally; by 2030, it is predicted that near 50% of the population will be obese, with half of them suffering from severe obesity [3, 4]. In line with obesity trends, approximately 35% of US adults have MetS [5, 6]. In Iran, the prevalence of metabolic syndrome is estimated to be around 31% in adult population [7]. In addition, Iranian women are more likely than women in western nations to suffer from this syndrome [8].

Over the last decade, evidence inspired by gut microbiota studies has revealed the possibilities and challenges of novel metabolic syndrome prevention and treatment strategies [9]. The human microbiota consists of over 100 trillion symbiotic microorganisms that live on and within humans, and it contains roughly 150 times the number of genes found in the human genome [10, 11]. There has been a long history of mutually beneficial interactions between the gut microbiota and the mammalian host, and this has led to the development of an intricately intertwined symbiotic relationship that affects a wide range of physiological functions [12]. To understand the rise in the metabolic syndrome prevalence, one must consider the rapid changes in our environment, which have a negative impact on factors such as sedentary behavior and dietary habits [13]. Apart from several other factors including genetics, diet is considered to be the most influential factor affecting the alterations in the diversity and composition of gut microbiota [14, 15]. These factors, by mediating alteration in the gut microbiome composition, may have an effect on the immune and metabolic systems, thereby influencing the risk of MetS [16]. The gut microbiota composition of patients with MetS differs from that of healthy individuals, which has been linked to changes in intestinal permeability, inflammation, obesity, and insulin resistance [17, 18]. Dysbiosis, defined as an imbalance of gut microbiota, is implicated in the development of the metabolic syndrome [19]. Dysbiosis results in a loss of microbial diversity, the eradication of beneficial microorganisms, and the spread of potentially pathogenic microorganisms [20]. The role of gut dysbiosis in the development of immune system dysfunction, cardiovascular disease, obesity, diabetes, metabolic syndrome, asthma, and inflammatory bowel disease has been examined extensively in many studies [19, 21].

Diet plays a crucial role in the development and composition of the gut microbiota. Various dietary factors influence the gut microbiota. Among others, the quantity and balance of macronutrients (carbohydrates, protein, and fat) have attracted a particular attention [22]. Dong et al. found that a calorie-restricted high protein diet had beneficial effects on microbial diversity and alteration in *Akkermansia spp*. and *Bifidobacterium spp*., as well as the loss of *Prevotella spp*., when compared to baseline [23]. On the other hand, a high-carbohydrate diet has been linked to dysbiosis and an increase in anaerobic pathogen species, most notably *Bacteroides* [24]. No specific diet has been recommended to manage patients with MetS so far. Several studies have demonstrated that the Mediterranean and DASH diets are effective at reducing insulin resistance and other components of metabolic syndrome [25, 26]. However, none of these diets have focused on the dietary macronutrient composition. Despite the worldwide recommendation on reduced fat intake, the prevalence of this syndrome has increased [27]. Therefore, it seems that the advice on low fat diets, in spite of their beneficial effects on some components of this syndrome, might not be an appropriate choice for managing metabolic syndrome [28]. High-protein diets have also been linked to kidney dysfunction, acidosis, and insulin resistance [29]. However, dietary carbohydrate restriction might be a suitable choice because earlier studies have shown that consumption of this dietary pattern has been resulted in improved components of MetS, even in the absence of weight loss [30]. Furthermore, low-carbohydrate diets outperform low-fat diets in terms of weight loss and adipose tissue reduction [31, 32]. This is particularly relevant in Middle Eastern countries, where people get more than 60% of energy from carbohydrates, in particular from refined sources [33]. High carbohydrate intake has also been blamed as one of the primary causes of the high prevalence of metabolic syndrome in Iranians [34]. In this regard, Rajaie et al. conducted a randomized crossover clinical trial in which they applied a carbohydrate-restricted diet by substituting dietary fats; this regimen contained 43–47% carbohydrate and 36–40% dietary fat. After 3 months of follow-up, a moderate-restricted carbohydrate diet reduced blood pressure, waist and hip circumferences, and the prevalence of the metabolic syndrome [35]. To the best of our knowledge, no earlier study has examined the effect of such dietary pattern on the gut microbiome composition in patients with metabolic syndrome. Understanding the diversity and composition of gut microbiome will aid researchers in developing novel MetS prevention and treatment strategies. As a result, the aim of this study is to (i) determine the effect of a moderately restricted carbohydrate diet on gut microbiota composition and metabolic parameters in women with metabolic syndrome and (ii) determine whether these potential changes in the gut microbiota will be sustained during a subsequent six-month weight maintenance phase.

## Material and methods

The present study is a parallel two-phase randomized controlled clinical trial that will be conducted at Shariati Hospital in Tehran, Iran. All participants must complete and sign an informed written consent form prior to completing their registration (Supplementary file, section A). Ethical approval has been obtained by the Bioethics Committee of Tehran University of Medical Sciences (No. IR.TUMS.MEDICINE.REC.1400.200).

### Study population

The current single-blind randomized controlled trial is a two-phase community-based research project. Participants will be recruited through a popular online advertising program rather than a health care center or hospital. This will be done to better reflect population diversity and produce more generalizable results across populations.

### Inclusion criteria

This study will be conducted on adult women with metabolic syndrome who have body mass index (BMI) greater than or equal to 25 and aged 20–50 years. MetS was defined as having three of the five conditions listed in the Adult Treatment Panel III guidelines from the National Cholesterol Education Program (NCEP-ATP III) [36]: (1) waist circumference of more than 88 cm (35 inches), (2) serum triglyceride (TG) level greater than 150 mg/dL, (3) serum high-density lipoprotein cholesterol (HDL-C) level of less than 50 mg/dL, (4) blood pressure greater than 130/85 mm Hg, and (5) fasting plasma glucose (FPG) levels greater than 100 mg/dL. Patients who reside in Tehran will be included in the study to minimize loss to follow-up. This study will only include women because it has been demonstrated that women are more likely than men to maintain dietary changes and adhere to the prescribed diet regimen after participating in a dietary intervention trial [35, 37].

### Exclusion criteria

Patients who meet the following criteria will be excluded from the study: (1) pregnancy, breastfeeding, or planning to become pregnant in the near future; (2) being current smokers or using other tobacco such as hookah; (3) evidence of some pathologic conditions such as liver, kidney, thyroid, and gastrointestinal tract diseases as well as suffering from diabetes, rheumatoid arthritis, lupus, severe infection, and trauma; (4) weight loss history surgery; (5) having a severe allergy to specific foods; (6) have been on a special diet or taken weight loss medication for three months prior to the study; and (7) consumed antibiotics, pre- or probiotic products or supplements 3 months prior to enrollment. We will also exclude postmenopausal women, participants who are unwilling to continue the intervention and have poor adherence to the prescribed (their dietary records show that their intake deviates more than 300 kcal from the prescribed amount, or dietary records show that the recommended macronutrient composition is not followed), and those who become infected with COVID-19 during the intervention. Figure 1 presents a schematic representation of the overall research plan.

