### Compliance

To assess how well participants adhere to their diets, their dietary intakes will be recorded once every 2 weeks in the first phase and every 4 weeks in the second phase by telephone interview. A sample of dietary recall format is provided in Supplementary file, section C. In total, participants are going to complete 12 dietary records (six in the first phase and six in the second phase). Participants will be asked to report their dietary intakes using household measures in order to complete the dietary recalls. Then, we will convert household measures to grams using the booklets provided. Participants’ total dietary intakes will be assessed using the average of all dietary recalls taken over the duration of the intervention. Total energy intake, macronutrients, and micronutrients will be computed from the dietary recalls using Nutritionist-IV software (First Databank, San Bruno, CA, USA) modified for Iranian dishes. We will also send text messages and make phone calls to participants throughout the study to increase compliance and prevent forgetfulness of diet principles.

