### Biochemical assessments

A blood sample will be taken from each patient’s venous blood at the study baseline, end of the first phase (after 3 months), and end of the second phase of the study (after 9 months) following 12 h of fasting. We will use a portion of the blood sample to evaluate glucose levels and lipid profile. The remaining serum will be kept at – 80 °C until it is further analyzed for insulin levels. Plasma glucose and lipid profile concentrations (TC, HDL, LDL, and TG) will be determined via an enzymatic colorimetric method using commercial kits. Finally, the serum insulin concentrations will be examined using electrochemiluminescence (ECL) method. We also will determine insulin resistance (HOMA-IR) and quantitative insulin-sensitivity check index (QUICKI) formulas.

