### Statistical analysis

All statistical analyses will be carried out using the SPSS software version 25 (SPSS Inc., Chicago, IL, USA). For addressing non-adherence, the intention-to-treat (ITT) analysis will be applied [41]. Moreover, we will apply the last observation carried forward method (LOCF) to handle missing values [42]. In order to determine the normal distribution of variables, we will use the Kolmogorov-Smirnov test, histogram, and Q-Q plot. We will log transform (ln) the data, if necessary, to achieve normal distribution. Data will be presented as mean ± standard deviation (SD) for continuous variables and as percentages for categorical variables. Chi-square test and independent samples *t*-test will be used for comparing continuous and categorical variables between the two groups, respectively. We also will use the paired-sample *t* test for within-group comparisons. Repeated measures analysis of variance will be employed to determine the impact of the intervention on the outcome variables. These analyses will examine the effects of the intervention, time, and the interaction between time and intervention. Any potential differences in baseline levels of outcome variables, dietary intakes, and physical activity will be controlled in these analyses. Statistical significance will be defined as *P* values less than 0.05.

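### The protocol excludes randomised women for unwillingness or poor adherence and for COVID-19 infection and never says they stay in follow-up, which conflicts with its intention-to-treat analysis

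*Protocol article*

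**What the plan says.** The Exclusion criteria section of the protocol article begins with conditions that can be checked at entry. It then adds "participants who are unwilling to continue the intervention and have poor adherence to the prescribed" diet. Poor adherence means that "their intake deviates more than 300 kcal from the prescribed amount", or that "dietary records show that the recommended macronutrient composition is not followed". The same sentence also excludes "those who become infected with COVID-19 during the intervention". The section introduces its list as reasons for exclusion from the study, not as reasons to stop the diet.

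Adherence is judged from records made after allocation. Under Compliance, "their dietary intakes will be recorded once every 2 weeks in the first phase and every 4 weeks in the second phase", six recalls per phase.

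Under Statistical analysis, "For addressing non-adherence, the intention-to-treat (ITT) analysis will be applied", and "we will apply the last observation carried forward method (LOCF) to handle missing values". Under Biochemical assessments, blood is drawn at baseline and at the "end of the first phase (after 3 months), and end of the second phase of the study (after 9 months". No section says that a woman excluded after allocation is still measured or still analysed.

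**The concern.** ITT compares all randomised women in the group to which they were allocated, whatever they went on to eat. A rule that excludes women for what they ate works against that, and here both rules address the same problem, non-adherence. Removal for COVID-19 infection is also a post-randomisation exclusion. It is inconsistent with ITT in general, although the ITT sentence itself names only non-adherence.

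Adherence is observed after allocation and the two arms follow different diets, so removal could differ by arm. The Background section puts carbohydrate intake in Middle Eastern countries above 60% of energy. From there, reaching the top of the control band (55%) takes a cut of more than 5 points, and reaching the top of the restricted band (45%) a cut of more than 15. The macronutrient criterion has no stated tolerance. Heavier removal in the restricted arm is therefore plausible, though the document gives no rates. If it happened and those women were dropped, the comparison would be between selected groups.

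**Working it through.** **1. The plan's own figure.** Inputs from Sample size calculation: two-sided α = 0.05, power 80%, σ = 3.5 (SD of HDL-C concentrations), d = 2.5, drop-out 10%.

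n = 2 × (1.960 + 0.842)² × 3.5² / 2.5² = 30.77, so 31 per arm; 31 / 0.9 = 34.4, so 35. The plan's 35 is reproduced. The reserve is 35 − 31 = 4 women per arm for losses of every kind. No separate allowance is made for adherence or COVID-19 removals, and Strengths and limitations already says the pandemic could raise loss to follow-up.

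**2. If removed women leave the analysis: bias.** With a fraction r of an arm removed and D = mean of retained women minus mean of removed women, the retained mean exceeds the full-arm mean by r × D. With the same D in both arms, the arm difference shifts by (r₁ − r₂) × D. Both r and D are assumptions. The D values are 0.5 and 1 times 3.5, which is an SD of concentrations and not of change, so they only set a scale.

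| Removed, arm 1 / arm 2 | D = 1.75 | D = 3.5 |
|---|---|---|
| 20% / 10% | 0.175 (7% of 2.5) | 0.35 (14%) |
| 30% / 10% | 0.35 (14%) | 0.70 (28%) |
| equal | 0 | 0 |

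**3. If removed women leave the analysis: power.** Power = Φ(2.5 / (3.5 × √(2/n)) − 1.960). It is 84.8% at n = 35, 80.9% at 31.5 (10% lost), 76.2% at 28 (20%) and 70.5% at 24.5 (30%). These losses do not arise if the women stay in the analysis.

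**4. If they stay in but are not measured.**
- Removed before the 3-month visit: baseline is the only value, so LOCF sets change to zero at 3 and 9 months. With a fraction r so removed in each arm, a difference of 2.5 among measured women becomes (1 − r) × 2.5, which is 2.25, 2.00 or 1.75 at r = 10%, 20% or 30%.
- Removed in phase II: the 3-month value is kept and copied to month 9. The 3-month comparison is untouched, but the woman is recorded as perfectly stable over the period in which stability is the question.

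**5. If they are kept and measured.** Suppose the fraction r has no benefit at all (an assumption). With 35 per arm and an effect of (1 − r) × 2.5, power is 76.7%, 66.7% or 55.2% at r = 10%, 20% or 30%. This is lower than the 80.9%, 76.2% and 70.5% in step 3.

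**6. Can adherence be judged on all recalls together?** A perfectly adherent woman in the restricted arm eats 42–45% carbohydrate in phase I and 52–55% in phase II. Her mean over 12 recalls is (6 × 42 + 6 × 52) / 12 = 47% to (6 × 45 + 6 × 55) / 12 = 50%, outside both bands. A perfectly adherent control woman stays at 52–55%. A pooled mean would misclassify one arm only.

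**The case against.** The exclusion section governs participation and the analysis section governs analysis. Since the latter names non-adherence as the reason for ITT and adds LOCF, the two can be read together: a woman is discontinued but stays in the analysis with carried-forward values. This reading is possible. A reader might infer that the two rules can never both apply to the same woman, or that the authors certainly intend to drop non-adherers from the analysis; the text does not establish either. The reading still gives a poor result, because ITT would then rest on the imputed values in step 4. Requiring unwillingness and poor adherence together does not help either, since the removal would still come after randomisation.

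Three further objections stand:

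- **COVID-19.** A reader might infer that these removals bias the arm comparison. The document gives no reason why infection should differ by arm, so the bias argument rests on adherence.
- **Unequal removal.** It is plausible but not shown. The 300 kcal rule is the same in both arms, the carbohydrate and fat bands have equal widths, and the phase II diet is the same for everyone.
- **Power.** A reader might infer that lost power is the main harm. It applies only if women leave the analysis, and steps 3 and 5 show that keeping non-adherers may cost more power than dropping them.

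The full protocol may say more about follow-up after discontinuation. That does not settle the point, because the article itself states exclusion from the study and ITT side by side.

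**Conclusion.** The point holds. The article excludes randomised women for events after allocation, does not keep them in follow-up, and states ITT for one of those events. Followed as written, it gives either an analysis that is not ITT or one that relies on LOCF values for women who could have been measured.

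The size cannot be computed from the document. Under the assumed removal rates and outcome gaps, dropping the women shifts the HDL-C difference by 0.18–0.70, or 7–28% of the planned 2.5, and by nothing if rates and gaps are equal in both arms. Under LOCF, removal of 10–30% before the 3-month visit shrinks 2.5 to 2.25–1.75. For phase II removals, the damage is to the 9-month stability question. This should be corrected; the conflict is in the text, and only its effect is uncertain.

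**What to change.** 1. Under Exclusion criteria, delete unwillingness to continue, poor adherence and COVID-19 infection during the intervention as reasons to remove randomised women. Keep the remaining items as entry criteria.
2. State that these women, unless they withdraw consent, are measured at the planned 3- and 9-month visits and analysed in their allocated group.
3. Use the 300 kcal and macronutrient criteria only to define a secondary per-protocol analysis. Apply them to the mean of the six recalls within each phase, against the diet prescribed for that phase.
4. Add a sensitivity analysis without women infected with COVID-19.

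The cost is revised wording in two sections, up to two already planned visits for each woman who would have been removed, and two secondary analyses on data already collected. Trial status says recruitment began in December 2021 and is ongoing, so this is a modification of a running trial. It must be communicated and entered in the registry, as that section provides, and women already removed may have missed their 3-month measurement. The main estimate may be diluted, and its power may be lower than after dropping non-adherers; the per-protocol analysis will show how far the results differ. The justification is freedom from selection bias.

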### Sample size calculation

Using a type I error of 5% (*α* = 0.05) and a type II error of 20% (*β* = 0.20, power = 80%), and serum HDL-C concentrations as the key variable, the sample size in this study was calculated using the following formula, which has been proposed for parallel clinical trials:$$n=\frac{2\left[{\left({\textrm{Z}}_{1-\frac{\alpha }{2}}+{\textrm{Z}}_{1-\beta}\right)}^2\times {\upsigma}^2\right]}{{\textrm{d}}^2}$$

*n* = sample size for each group.

*σ* = The variance (SD) for mean HDL-C concentrations was as 3.5, which was calculated using the average SDs reported for serum HDL-C in Rajaie et al. study [35].

*d* = The minimal clinically important difference for HDL-C was set at 2.5, based on previous research [38].

Overall, using this formula and assuming a 10% drop-out rate in each group, we will require a sample size of 35 subjects in each group.

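### Women are to be excluded for events that occur after randomisation, which conflicts with the declared intention-to-treat analysis and leaves the analysis set undefined

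*Protocol article*

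**What the plan says.** The protocol article's Exclusion criteria section opens with characteristics that can be checked at screening, such as pregnancy, smoking, disease and recent antibiotics. In the same paragraph, and with the same verb, it then adds women who do not wish to go on with the diet *and* who show "poor adherence to the prescribed (their dietary records show that their intake deviates more than 300 kcal from the prescribed amount". A second, alternative test of poor adherence is that "dietary records show that the recommended macronutrient composition is not followed". The list ends with "those who become infected with COVID-19 during the intervention".

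The Statistical analysis section says: "For addressing non-adherence, the intention-to-treat (ITT) analysis will be applied". The next sentence assigns missing values to LOCF.

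Three other sections matter here:

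- **Compliance:** dietary intake is recorded by telephone every 2 weeks in phase I and every 4 weeks in phase II, so adherence is known only once a diet has been assigned.
- **Sample size calculation:** 35 per group, "assuming a 10% drop-out rate in each group".
- **Study design:** outcome assessors are blinded; no blinding of participants or dietitians is stated.

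No section says whether an excluded woman is still measured or still analysed.

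**The concern.** One section removes women for non-adherence, and another names ITT as the remedy for the same non-adherence. A reader cannot tell which women will be analysed, for any outcome.

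Randomisation makes the arms comparable as allocated. Selecting women afterwards, on behaviour that the allocated diet can influence, gives up that protection. The result would describe women who kept to their diet but could be reported under the ITT label.

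The macronutrient rule adds a particular risk, because adherence is judged against a different target in each arm. Exclusions also draw on a loss allowance of only 10%, in a trial whose limitations section already warns that the pandemic may increase losses.

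**Working it through.** **1. When each exclusion can occur**

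| Ground | Earliest time it can be known |
|---|---|
| Unwilling to continue | after the diet has started |
| Intake more than 300 kcal off the prescription | first dietary recall after allocation |
| Macronutrient composition not followed | first dietary recall after allocation |
| COVID-19 during the intervention | after the diet has started |

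The wording joins unwillingness and poor adherence with *and*. They may be one joint ground or two separate ones. Both readings are exclusions after randomisation.

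**2. The plan's own sample size**

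Inputs (Sample size calculation): two-sided α = 0.05, power 80%, SD 3.5, d = 2.5 for HDL-C.

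n = 2 × (1.960 + 0.842)² × 3.5² / 2.5² = 2 × 7.849 × 12.25 / 6.25 = 30.77, rounded up to 31 per group.

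With 10% loss: 31 / 0.9 = 34.4, rounded up to 35. The stated figure reproduces.

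**3. Reading A: excluded women leave the analysis**

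Number analysed per arm = 35 × (1 − e), with exclusion rate e equal in both arms. The 20% and 30% rates are assumptions. Power is for a two-sided comparison at d = 2.5 and SD = 3.5.

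| e | n per arm | Power, t-test | Power, normal approximation |
|---|---|---|---|
| 0% | 35 | 83.8% | 84.8% |
| 10% | 31.5 | 79.7% | 80.9% |
| 20% | 28 | 74.7% | 76.2% |
| 30% | 24.5 | 68.7% | 70.5% |

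**4. Reading A: bias**

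Suppose the diets do not differ and excluded women have an HDL-C change worse by D than retained women. The retained mean in an arm then exceeds the full-arm mean by e × D, so the bias in the comparison is (e_MRC − e_NWL) × D. Its standard error is 3.5 × √(1/n₁ + 1/n₂). All rates and values of D are assumptions.

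| Excluded, MRC v NWL | D | Bias | Standard error | Two-sided type I error |
|---|---|---|---|---|
| 10% v 10% | any | 0 | – | 5% |
| 20% v 10% | 2.5 | 0.25 | 0.909 | 5.9% |
| 20% v 10% | 5 | 0.50 | 0.909 | 8.5% |
| 30% v 10% | 2.5 | 0.50 | 0.943 | 8.3% |
| 30% v 10% | 5 | 1.00 | 0.943 | about 18.6% |

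Unequal rates are plausible for this reason. The Background section says that in Middle Eastern countries "people get more than 60% of energy from carbohydrates". From 60%, the MRC target of 42–45% needs a fall of 15 to 18 points (60 − 45, 60 − 42). The NWL target of 52–55% needs 5 to 8 (60 − 55, 60 − 52).

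**5. Reading B: excluded women stay in through LOCF**

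A woman removed before month 3 carries her baseline forward, so her change is zero. With share e removed in each arm, a true difference of 2.5 shrinks to 2.5 × (1 − e). With 35 per arm and SD kept at 3.5:

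| e | Difference | Power, t-test | Power, normal approximation |
|---|---|---|---|
| 10% | 2.25 | 75.5% | 76.7% |
| 20% | 2.00 | 65.4% | 66.7% |
| 30% | 1.75 | 54.1% | 55.2% |

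A woman removed in phase II carries her 3-month value to month 9. She then appears perfectly stable by construction, and stability is the question phase II asks.

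**The case against.** The strongest defence is that exclusion here means withdrawal from the diet, with the withdrawn women analysed in their arm through LOCF. That would reconcile the two sections, and the flow charts, which are not shown, might support it. The text does not state it, however. Even if it is meant, step 5 shows that outcomes which could have been measured are replaced by carried-forward values. The defence changes the fault without removing it.

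The second defence concerns bias, and much of it stands. A reader might infer that exclusion is bound to differ between arms. The documents do not support that. The intake above 60% describes a region, not the enrolled women. The 300 kcal rule, the calorie deficit and the 3-point width of the carbohydrate range are the same in both arms. Nothing suggests that COVID-19 depends on diet, so that exclusion mainly costs numbers. With equal rates and equal prognosis the bias is zero.

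A reader might also infer that the macronutrient rule would remove most of the trial. That would need a spread of intakes that the article does not give, and a reading of the rule under which any value outside the range, however slight, excludes. The text does not say this, and if unwillingness is also required, off-target intake alone would not be enough.

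Third, retention does not protect power. If retained women show no change, the power in step 5 is lower than in step 3 at the same rates. This is correct, and it is why power is not the argument for the change.

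**Conclusion.** The point holds as a contradiction between the Exclusion criteria and Statistical analysis sections. It is direct for non-adherence, which is both a ground for exclusion and the stated reason for using ITT. Excluding women for COVID-19 after allocation is a further departure from ITT. This is not detail that an article leaves to a fuller document, because the article states both rules. On either reading, some randomised women are not analysed on their real outcomes in the arm assigned.

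The size of any bias is unknown. Unequal exclusion is plausible, given the different targets and the absence of stated participant blinding, but it is not established. The type I error figures illustrate assumed rates and are not predictions. The sample size contains no arithmetic error. At the plan's d = 2.5 and SD = 3.5, its 10% allowance gives about 80% power; assumed equal exclusion of 20% or 30% would give about 75% or 69%. It should be corrected because the analysis set for every outcome depends on it.

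**What to change.** Reconcile the two sections as follows:

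- Limit the exclusion criteria to characteristics that can be established before randomisation.
- State that every randomised woman is invited to the 3- and 9-month measurements, whatever her adherence or COVID-19 status, and is analysed in the arm assigned.
- Record diet discontinuation, deviation and COVID-19 as events.
- Use the 300 kcal, macronutrient and COVID-19 rules only to define a supplementary per-protocol or sensitivity analysis, labelled as such. State there whether unwillingness and poor adherence are joint or separate grounds.

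This concerns who is measured and analysed; it alters no diet or clinical rule. The cost is protocol wording and the continued measurement of women who stop the diet. The ITT effect, and possibly the power, may be smaller than among adherers, and the team should accept that openly.
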